### Phase II: Quantitative Phase

#### Activity 1: Questionnaire Development and Validation

##### Overview

In activity 1, we will develop a questionnaire of an acceptable PBD for controlling hypertension, according to the qualitative data in phase I. The quotations from raw data will become questionnaire items, themes will become scales, and codes will become variables. A Likert score will be used for measurement (range of 1 to 4 points), which will determine the levels of expectations and acceptability. Based on the scores of the items or the summed scores, expectations and acceptability can be categorized into the following 3 categories: affordable, accessible, and achievable. Categorization will be performed using a statistical formula. If the data are normally distributed, the grade level will be based on the mean value; otherwise, the median will be used (X < mean/median – 1 SD; mean/median – 1 SD < X < mean/median + 1 SD; mean/median + 1 SD < X).

The questionnaire will have the following 2 sections: (1) sociodemographic characteristics of hypertension and (2) acceptable PBD for controlling hypertension. The instructions and descriptions of the definition, concept, and criteria of a PBD will be provided at the beginning of the questionnaire. The Pender Health Promotion Model will guide the questionnaire’s qualitative analysis and item design. After performing a member check and assessing face and content validity with an expert committee, we expect the final version of the questionnaire. The expert committee will include investigators with expertise in qualitative research (HR), statistical analysis (FK), public health (TS), and research methodology ([name] and IR).

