##### Validation and Reliability

A cognitive debriefing involving 10 people to further assess the face and content validity of the questionnaire will be performed (5 expert nurses on hypertension and 5 nutritionists). Feedback will be discussed by the expert committee, and it will determine the appropriateness and completeness of the questionnaire and ethical considerations in the process. The next analysis step is the COSMIN (consensus-based standards for the selection of health measurement instruments) checklist developed in an international Delphi study to estimate the quality of selected measurement instruments. It measures internal consistency, reliability, measurement error, content validity (as well as face validity), structural validity, hypothesis testing, cross-cultural validity (the 3 aspects of construct validity), criterion validity, and responsiveness. Based on the checklist, items will be sorted by experts in the group to establish face, content, and construct validity in activity 1. The duration to finish the questionnaire is estimated to be less than 30 minutes. Further validation of the questionnaire will be conducted in activity 2. Cronbach alpha will be applied to prove the internal consistency (0.70 or higher is considered as good) of the expectations and acceptability questionnaire. Exploratory factor analysis using principal component analysis will be performed to examine the structural validity of the expectations and acceptability questionnaire separately.

In addition, the Kaiser-Mayer-Olkin test of sampling adequacy, the Bartlett test of sphericity, and the scree plot will be used to check the unidimensionality of the expectations and acceptability questionnaire. The convergence criteria will be set at an eigenvalue above 1. Construct validity (hypothesis testing) will be tested when comparing the responses to the expectations or acceptability of 1 item (yes or no). We hypothesize that the highest tertile expectation will be associated with willingness measured by a repeat measurement value of at least 2.0. The highest tertile acceptability will be related to willingness measured by a repeat measurement value of at least 3.0. It is also hypothesized that expectations and acceptability will correlate at a coefficient of at least 0.4. One-month intrarater test-retest reliability will be assessed in a random sample of at least 50 older people throughout the data collection period in activity 2.

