##### Participants

The criteria for recruiting our representative sample are as follows: (1) farmers aged 20-65 years from other parts of East Java Province, Indonesia (citizens) living in 3 PHCs in Jember; (2) residents living in 3 PHCs in Jember; (3) those with grade I/II hypertension according to the JNC VIII criteria; (4) those who attend the IHC for NCDs in the community; and (5) those having and living with family for care provision. We will exclude (1) farmers with psychiatric disorders that may impair their ability to answer or complete the questionnaires and (2) farmers with cognitive impairment.

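### KMO and Bartlett do not test unidimensionality, the eigenvalue-above-1 rule can over-extract, and the retest sample of older people conflicts with a survey of farmers aged 20-65

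*Protocol article*

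**What the plan says.** All references are to the protocol article, Phase II.

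- **Structure.** Under Activity 1, Validation and Reliability: "Exploratory factor analysis using principal component analysis will be performed to examine the structural validity", run separately for expectations and for acceptability. The same section states that "the Kaiser-Mayer-Olkin test of sampling adequacy, the Bartlett test of sphericity, and the scree plot will be used to check the unidimensionality", and then: "The convergence criteria will be set at an eigenvalue above 1".
- **Internal consistency.** "Cronbach alpha will be applied to prove the internal consistency (0.70 or higher is considered as good").
- **Test-retest.** One-month reliability is assessed in "a random sample of at least 50 older people throughout the data collection period" of activity 2.
- **Scoring.** The Activity 1 Overview turns themes into scales measured on 1 to 4 points. It categorizes expectations and acceptability as follows: "Based on the scores of the items or the summed scores".
- **Population.** Activity 2, Participants, admits "farmers aged 20-65 years from other parts of East Java Province, Indonesia (citizens) living in 3 PHCs in Jember", with no older subgroup. Activity 2, Sample Size Estimation, gives 263 respondents.

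**The concern.** Unidimensionality means that one latent dimension accounts for the correlations among the items. Bartlett's test asks whether the correlation matrix differs from an identity matrix. KMO asks whether correlations are large relative to partial correlations. Both say whether factoring is worthwhile and neither counts factors, so the sentence gives them a purpose they cannot serve.

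The count is left to the scree plot, read by eye, and to the eigenvalue rule. That rule governs how many components are kept. It has nothing to do with convergence, and in finite samples it can keep components that are only noise.

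A summed score is easy to interpret only when its items share a dimension. The acceptability categories feed the survey's chi-square and logistic models, and acceptability is also named as a trial outcome in the Activity 3 Overview. If the rule splits a sound scale, or if a good KMO is reported as evidence of one dimension, the score rests on the wrong argument.

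The second issue is separate. A retest coefficient from older people need not describe a survey population that starts at age 20.

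**Working it through.** **1. The sample size used.** The article gives 263, power 0.90, two-sided alpha .05 and a 10% difference in proportions. Assuming a null of 0.50 (not stated), n = (1.960 + 1.282)² × 0.25 / 0.10² = 262.7, i.e. 263. An exact one-sample binomial test of 0.50 against 0.60 has power 0.902 at 263. The figure is reproduced and not disputed. It is taken as the sample for the factor analysis, because further validation is placed in activity 2.

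**2. Assumptions.** The article gives neither item count p nor loadings λ. The range examined is p = 10 to 30 and λ = .4 to .8, with four-point items.

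**3. Bartlett and KMO on data that are not one-dimensional.** Take two uncorrelated factors with 10 items each at λ = .6, continuous for simplicity.
- Within a block, r = .36, so ln|R| = 2 × [ln(1 + 9 × .36) + 9 × ln(.64)] = 2 × (1.4446 − 4.0166) = −5.144.
- Bartlett: χ² = −[n − 1 − (2p + 5)/6] × ln|R| = (262 − 7.5) × 5.144 ≈ 1,309.
- Degrees of freedom are 20 × 19 / 2 = 190, so the null mean is 190 and the null SD is √380 ≈ 19.5.

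The test is overwhelmingly significant although there are two factors. In simulations of four-point items (n = 263, 1,000 runs per scenario, two or three factors, factor correlation 0 or 0.3), Bartlett gave P<.05 and KMO exceeded .6 in 100% of runs, with mean KMO from .75 to .88. A separate simulation found KMO above .6 in nearly all such runs.

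**4. The eigenvalue rule when one factor is true.** In the population the first eigenvalue is 1 + (p − 1)λ² and all others are 1 − λ², below 1. The rule would then be right. Sampling error spreads the remaining eigenvalues up to roughly (1 − λ²)(1 + √(p/n))², the Marchenko-Pastur upper edge. If that exceeds 1, extra components are expected.

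| Items | Loading | Approximate edge | Mean kept (simulated) | Exactly one kept |
|---|---|---|---|---|
| 10 | .5 | .75 × 1.43 = 1.07 | 1.70 | 35% |
| 10 | .6 | .64 × 1.43 = 0.91 | 1.01 | 99% |
| 10 | .7 | .51 × 1.43 = 0.73 | 1.00 | 100% |
| 20 | .5 | .75 × 1.63 = 1.22 | 4.46 | 0% |
| 20 | .6 | .64 × 1.63 = 1.04 | 2.09 | 18% |
| 20 | .7 | .51 × 1.63 = 0.83 | 1.01 | 99% |
| 30 | .5 | .75 × 1.79 = 1.34 | 7.61 | 0% |
| 30 | .6 | .64 × 1.79 = 1.15 | 4.32 | 0% |
| 30 | .7 | .51 × 1.79 = 0.91 | 1.29 | 72% |

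The edge assumes continuous items. Four-point coding lowers the correlations, which explains the last row: with continuous items the rule kept one component there in 99% of runs. Separate simulations gave 4.3 to 4.5 components for 20 items at .5 and 2.0 to 2.1 at .6. In those settings parallel analysis found one factor in every run.

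**5. The eigenvalue rule when several factors are true.** In the two- and three-factor scenarios it never kept just one component (0% of runs). Its error is splitting.

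**6. The scree plot.** The ratio of first to second eigenvalue, a numerical stand-in for the plot, was 2.9 to 17.8 with one factor and 1.1 to 1.8 with two or three. The plot therefore does carry the information. Factor correlations above 0.3 were not examined, and the contrast would be expected to narrow there.

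**7. The retest population.** Validation and Reliability draws the retest sample from older people during activity 2. Activity 2, Participants, defines farmers aged 20-65 and names no older group. Activity 2, Sample Size Estimation, also refers to elderly people and a smart nursing home. That suggests leftover wording but does not settle which population is meant.

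**The case against.** The strongest reply is that principal components, eigenvalue above 1 and a scree plot form a conventional SPSS sequence, and that the parts should be judged together. Much of this stands.

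- A reader might infer that the planned checks as a set cannot reveal dimensionality. The documents do not support that, because the same sentence names the scree plot, which separated the simulated cases. Its lack of a stated reading rule is something a full protocol or analysis plan may supply.
- A reader might infer that the rule always splits a single factor at 263 respondents. It does not: the result depends on item count and loadings, which the article does not give, and the rule does well with strong loadings or a short scale.
- A reader might infer that the eigenvalue rule would pass a multi-factor scale as one. No simulated run showed this. Only KMO and Bartlett pass on such data.
- A reader might infer that all reliability evidence comes from older people. Only the test-retest sample is so described; Cronbach alpha carries no such limit.

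It is also fair that several scales are already foreseen and that scoring by item remains open, so a single total is not fixed. A biased retest coefficient is possible but not established.

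What does not stand is the purpose given to KMO and Bartlett, the convergence label, and the age wording. Cronbach alpha does not fill the gap. It reached .70 in 99.8% to 100% of runs with two factors or with three factors correlated 0.3, though in only 0.4% to 19% with three uncorrelated factors.

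**Conclusion.** The point holds in a limited form and is minor. KMO and Bartlett cannot support unidimensionality, and this does not depend on the assumed item count or loadings. That the eigenvalue rule over-extracts is conditional on them: the damage ranges from none (10 items at .6 or above, 20 items at .7) to several spurious components (20 items at .5, 30 items at .5 or .6). The conflict between older people and ages 20-65 is plain on the text and is a separate defect.

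The reach is the questionnaire, the survey models built on it, and acceptability as a trial outcome. Systolic and diastolic blood pressure, the main trial outcomes, are not touched.

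**What to change.** In Validation and Reliability:

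1. State that KMO and Bartlett are checks of factorability made before factoring, and remove them from the check of unidimensionality.
2. Replace the eigenvalue-above-1 rule, and the word convergence, with parallel analysis read together with the scree plot, separately for expectations and acceptability.
3. State that summed scores are formed per retained factor.
4. Describe the retest group as a random sample of at least 50 of all survey respondents, so that it matches Activity 2, Participants, and retest reliability describes the surveyed population.

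The cost is a few sentences and a short script for parallel analysis in addition to the standard SPSS output. No further respondents or data are needed. The evidence here for parallel analysis comes from one-factor data, so once the item count is known the script can also be run on simulated multi-factor data before the survey is analysed.

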#### Activity 2: Survey

##### Overview

In activity 2, we will conduct a survey to identify the prevalence of hypertension, the level of acceptability of a PBD, and the associated sociodemographic factors among farmers. We will use the questionnaire developed in activity 1. Written informed consent will be obtained, and each participant will be required to indicate agreement for participation before filling out the questionnaire and submitting it.

##### Setting

To obtain a representative sample according to the criteria that have been set, we will select 3 PHCs located in agricultural areas in Jember, East Java, Indonesia. The PHCs we have selected include Banjarsengon, Sukorambi, and Panti. There are quite a lot of farmers in the Panti area, with 14,322 active farmers having quite complex hypertension problems [22]. Farmers in Banjarsengon and Sukorambi also show a similar condition. These 3 PHCs are expected to have a sufficient number of farmers with hypertension who could respond and complete the questionnaire.

##### Participants

The criteria for recruiting our representative sample are as follows: (1) farmers aged 20-65 years from other parts of East Java Province, Indonesia (citizens) living in 3 PHCs in Jember; (2) residents living in 3 PHCs in Jember; (3) those with grade I/II hypertension according to the JNC VIII criteria; (4) those who attend the IHC for NCDs in the community; and (5) those having and living with family for care provision. We will exclude (1) farmers with psychiatric disorders that may impair their ability to answer or complete the questionnaires and (2) farmers with cognitive impairment.

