The agronursing approach to treat hypertension among farmers focuses on promotive and preventive measures to reduce the risk of disease occurrence or disease worsening from previous conditions [15]. Moreover, it focuses on the health status of individuals in carrying out their work (in this case, farmers who work in fields) in order to improve overall health (physically, mentally, and socially) [16]. The PBD concept is expected to be able to overcome the problem of hypertension among farmers in agricultural areas, which is synergistic with the culture and local wisdom of the agricultural population. Therefore, the objectives of this study are as follows: (1) to explore the health problem of hypertension among farmers and the characteristics of local food sources of vegetables and fruits that can be used in a PBD to manage hypertension; (2) to examine the prevalence of hypertension, the level of acceptability of a PBD, and the associated factors among farmers; and (3) to examine the effectiveness of a community-based nursing program for the management of hypertension using a PBD among farmers.

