#### Participants

The inclusion criteria for recruiting the purposive sample are as follows: (1) farmers aged 20-65 years from other parts of East Java Province, Indonesia (citizens) living in 3 PHCs of Jember; (2) residents living in 3 PHCs of Jember; (3) those with hypertension; (4) those who consume fruits and vegetables to control their blood pressure; (5) those who attend the Integrated Health Center (IHC) for noncommunicable diseases (NCDs) in the community; and (6) those having and living with family for care provision. We will exclude older people who are not citizens of Indonesia and those who are unwilling to be interviewed or unable to communicate clearly due to language problems. To obtain more insights on the acceptability of a PBD, the family members of eligible farmers with hypertension will be included in the interview. The inclusion criteria are as follows: (1) employment as a farmer; (2) age 45-65 years; (3) presence of grade I/II hypertension according to the Eighth Joint National Committee on Prevention, Detection, and Treatment of High Blood Pressure (JNC VIII) criteria; and (4) presence of relatives who stay in the same house with their parents or take care of their parents by helping them with preparing food or assisting them in daily routines. We will exclude farmers with hypertension having other chronic diseases (diabetes mellites, chronic kidney disease, heart disease, and stroke).

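### Criterion 1 for phase I and the survey, read as written, excludes farmers who originate from Jember, probably through a drafting slip

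*Protocol article*

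**What the plan says.** Two eligibility lists in the protocol article carry the same origin condition.

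- **Phase I, Participants**, criterion 1: "farmers aged 20-65 years from other parts of East Java Province, Indonesia (citizens) living in 3 PHCs of Jember".
- **Activity 2 (Survey), Participants**, criterion 1: "farmers aged 20-65 years from other parts of East Java Province, Indonesia (citizens) living in 3 PHCs in Jember".

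In the survey list, criterion 2 is a separate residence condition, "2) residents living in 3 PHCs in Jember". The list closes with "and (5) those having and living with family for care provision", so the items are joined by 'and'. The phase I list is joined in the same way before its sixth item. The survey list is introduced by "The criteria for recruiting our representative sample are as follows".

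The phase I section also contains a second inclusion list, placed after the sentence on family members. It covers employment as a farmer, age 45-65 years, grade I/II hypertension and relatives in the home, and it sets no condition on origin.

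**The concern.** Criterion 1 has two geographical parts: the farmer comes from elsewhere in the province, and the farmer lives in one of the three PHC areas. A farmer who was born in Panti and has always farmed there meets the second part and fails the first. If all criteria must be met, that farmer is ineligible for both the interviews and the survey.

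The study concerns "the characteristics of local food sources of vegetables and fruits that can be used in a PBD to manage hypertension", and its concept is described as "synergistic with the culture and local wisdom of the agricultural population". Farmers who originate from the area are natural informants on both. If they were left out, the qualitative findings and the acceptability estimates would describe a subgroup by origin, while the protocol would present them as describing the resident farmers.

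**Working it through.** The question is one of wording, so the main check sets the sections of the protocol article side by side.

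**Step 1: can criterion 2 readmit a farmer who fails criterion 1?** There are two ways to read the list.

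- *All criteria apply.* Criterion 2 repeats the residence part of criterion 1 and adds nothing. A farmer originating from Jember fails criterion 1 and is excluded.
- *Criteria 1 and 2 are alternative routes.* Anyone who meets criterion 1 already lives in the three PHC areas and so already meets criterion 2, which makes the geography of criterion 1 redundant. In addition, the farming occupation, the age range and citizenship stand only in criterion 1. Someone entering through criterion 2 would face none of these, which cannot be intended in a survey of farmers.

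The connective favours the first reading, and the second produces a worse list. Neither reading gives a coherent rule as the text stands.

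**Step 2: does any other section support an origin restriction?**

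| Section | What it implies about origin |
|---|---|
| Introduction, objectives | Speaks of farmers and local food sources, with no origin limit |
| Survey, Setting | "To obtain a representative sample according to the criteria that have been set, we will select 3 PHCs located in agricultural areas in Jember"; the choice rests on the areas' own farmers, for example 14,322 active farmers in Panti |
| Survey, Measures | Lists the sociodemographic items; place of origin is not one of them |
| Survey, Sampling Process | Simple random sample from farmers with hypertension on the Posbindu PTM list; no filter on origin |
| Activity 3 (RCT), Participants and eligibility criteria | Farmers with hypertension from the three PHCs; no origin limit |
| Conclusion | Benefit expected for farmers in Jember |

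None supports the restriction. Because origin is not among the listed survey variables, the survey as described could neither verify the criterion nor describe its effect afterwards.

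**Step 3: does any planned number depend on it?** The only figure in this part of the plan is the survey size of 263, for a 10% difference, two-sided α of .05 and power 0.90. The article gives no base proportion, so p0 = 0.50 against p1 = 0.60 is an assumption here.

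- One-sample normal approximation: n = [(1.960 × √(0.50 × 0.50) + 1.282 × √(0.60 × 0.40)) / 0.10]² = 258.5, rounded up to 259.
- Exact two-sided binomial test: power is 0.889 at n = 262 and 0.902 at n = 263. Over the sizes checked (245 to 284), 263 is the first to reach 0.90.

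The stated 263 is therefore reproduced under that assumption. Origin does not enter the calculation, so correcting the criterion leaves the number unchanged.

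**Step 4: can the extent of the exclusion be computed?** It would need the share of resident farmers with hypertension who come from elsewhere in the province. The article does not give it, and nothing in the article bounds it.

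**The case against.** The strongest reply is that no one would apply the text literally. Criterion 2 and the unfiltered Posbindu PTM list both suggest that all resident farmers were meant, and the described sampling process contains no step at which origin would be checked. The second phase I inclusion list has no origin condition either. This largely stands as an account of intent: the phrase is probably a slip, and nothing shows a deliberate choice to study in-migrants. It does not make the text harmless. An investigator who follows the criterion gets a sample that is not representative, and one who ignores it enrols people who fail a stated inclusion criterion. The second phase I list does not repair the first, and it has no counterpart in the survey section.

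A reader might also infer more than the article supports:

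- *That most target farmers are ineligible, or that 263 respondents could not be found.* No in-migrant share is given. The only farmer count is for Panti, whereas 263 is the target across three PHCs.
- *That the menu would come from in-migrants alone.* Family members are interviewed too, an earlier scoping review feeds the work, and the researchers formulate the diet. Even on the literal reading, participants live in the area and can report on the food available there.
- *That the trial is compromised.* Its eligibility criteria have no origin limit, and its sample size and blood pressure outcomes do not depend on this phrase.

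Finally, objectives 1 and 2 say farmers without naming Jember. The link to Jember's resident farmers comes from the setting, the trial population and the conclusion.

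**Conclusion.** The concern holds as an internal contradiction in operative eligibility text. Read cumulatively, criterion 1 in phase I and in the survey excludes farmers originating from Jember. That conflicts with the claim of a representative sample, the sampling frame, the list of survey variables, the trial population and the stated conclusions.

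The consequence is conditional. If the criterion is applied literally, the phase I farmer interviews and the survey's acceptability estimates would not represent the resident farmers they are meant to describe. How far they would depart cannot be stated from the article. The survey's 263 and the trial's eligibility and sample size are unaffected. The conclusion rests on reading the criteria as cumulative, which the connective and Step 1 support. A reader who prefers the other reading still faces a list that needs rewriting.

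**What to change.** In Participants under phase I and under Activity 2, delete the place-of-origin phrase from criterion 1 and merge criteria 1 and 2 into one. Possible wording: *farmers who are Indonesian citizens, aged 20-65 years and resident in the catchment areas of the three PHCs*.

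In phase I, also reconcile this with the second inclusion list, stating to whom each list applies and which age range holds for whom (20-65 or 45-65 years).

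If place of origin is of scientific interest, add it to the sociodemographic items under Measures rather than using it for selection.

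The cost is an edit to two lists, plus one questionnaire item if origin is recorded. No study visit or sample size changes.

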##### Sampling Process

Representative research respondents will be selected by collecting available data on public health services. Farmers with hypertension are listed as regular patients in the Posbindu PTM (Pos Pembinaan Terpadu Penyakit Tidak Menular) program of the public health services. The data obtained will be assessed in a random process to select respondents using a simple random sampling technique. We will use a randomizer application that is available online to select respondents. Respondents selected from the randomizer application will then be included in the list of research respondents. We will follow the activities of the Posbindu PTM program as well as meet with research respondents who have been selected to be able to collect research data. We will print out the questionnaire and give it to the research respondents to fill out. Our team will assist farmers in filling out questionnaires to ensure that the questionnaires given are filled out completely and accurately.

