## Results

This research has been funded by DRPTM Kementerian Pendidikan, Kebudayaan, Riset dan Teknologi Skema Riset Penelitian Dasar Unggulan Perguruan Tinggi (PDUPT) in 2022 (0277/E5/AK.04/2022). The research started in May 2022, and phase I of the study is scheduled to begin in May 2023, with a total research duration of 2 years. A model PBD for the management of hypertension is expected to be developed from using local food–related agronursing services. In 2022, we will collect data on hypertension and the characteristics of local food sources to manage hypertension, and formulate a PBD menu to treat hypertension among farmers. A thematic analysis of the qualitative data of farmers in the agricultural sector will be performed. In 2023, we will develop a questionnaire to assess the acceptability of a PBD to manage hypertension among farmers, the prevalence of hypertension, and the sociodemographic factors associated with hypertension among farmers. Furthermore, we will introduce a community-based nursing program for the management of hypertension using a PBD among farmers.

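### Activity 2 samples only known hypertensive farmers, so it cannot estimate hypertension prevalence or factors associated with hypertension; acceptability remains estimable

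*Protocol article*

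**What the plan says.** **What is promised.** The second study objective, at the end of the Introduction, is "to examine the prevalence of hypertension, the level of acceptability of a PBD, and the associated factors among farmers". The Overview of Activity 2 says "we will conduct a survey to identify the prevalence of hypertension, the level of acceptability of a PBD, and the associated sociodemographic factors among farmers". The prevalence aim also appears in the Objective, Methods and Results paragraphs of the Abstract, in the Study Overview under Methods, and in the Results section. The Abstract's Results paragraph and the Results section go a step further and promise "the prevalence of hypertension, and the sociodemographic factors associated with hypertension among farmers".

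**Who is sampled.** Under Activity 2, Participants, the third criterion requires "those with grade I/II hypertension according to the JNC VIII criteria" and the fourth requires "those who attend the IHC for NCDs in the community". Under Sampling Process, "Farmers with hypertension are listed as regular patients in the Posbindu PTM" programme, and the selection step reads "The data obtained will be assessed in a random process to select respondents using a simple random sampling technique".

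**What is measured and analysed.** Under Measures, the only hypertension variables are duration and grade. Under Sample Size Estimation, the survey is sized on a 10% difference in the proportion for expectations and acceptability, giving 263. Under Analysis Plan, the outcomes are expectations and acceptability; hypertension status is not an outcome.

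**The concern.** A prevalence is a count of cases over a count of everyone in the target population. A study of factors associated with a disease needs people with and without it. Here having the disease is a condition of entry, and it is also how the sampling list is made up. The document describes no screening step, no list of all farmers and no comparison group without hypertension.

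At stake are one of the three parts of objective 2 and a further result promised in two summaries. Data collection would run without any sign of trouble, and the gap would show only at reporting. By then the missing non-cases could not be recovered. A proportion computed from this sample and presented as prevalence among farmers would mislead readers about the burden of disease in the area.

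**Working it through.** **1. Inputs**
- Planned survey size 263, power 0.90, two-sided α 0.05, difference 10% (Activity 2, Sample Size Estimation).
- Hypertension required of every respondent (Activity 2, Participants, third criterion); sample drawn from listed hypertensive patients (Sampling Process).
- Hypertension figures in the Introduction: 35.8% among farmers in agricultural areas (which the article calls incidence), 36.1% among Indonesian farmers, 20.43% in East Java. Using 35.8% as a prevalence is my assumption.

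**2. The plan's own figure.** The article does not state a reference proportion. I assume a one-sample exact binomial test of 0.5 against 0.6, with α split equally between the tails. The smallest n with power of at least 0.90 is then 263 (power 0.902, actual α 0.048). The stated figure reproduces exactly, as a sample size for a proportion such as acceptability. It was not derived from a required precision for prevalence.

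**3. What the sample gives under the stated eligibility**
- Hypertensive respondents / all respondents = 263/263 = 100%, whatever the true prevalence.
- Respondents without hypertension = 263 − 263 = 0. Hypertension status does not vary, so no chi-square test, odds ratio or logistic model can be formed with it as the outcome.
- A larger sample from the same list changes neither result.

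**4. What it would take to keep prevalence.** Suppose n = 263 farmers are drawn regardless of blood pressure, with true prevalence p:
- 95% half-width = 1.96 × √(p(1 − p)/263)
- expected hypertensive respondents = 263 × p
- farmers to screen so as to keep 263 hypertensive respondents = 263 / p, rounded up

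| Assumed p | Half-width (points) | Hypertensive among 263 | To screen for 263 hypertensive |
|---|---|---|---|
| 20.43% | ±4.9 | about 54 | 1,288 |
| 35.8% | ±5.8 | about 94 | 735 |
| 36.1% | ±5.8 | about 95 | 729 |

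Written out at 35.8%: 1.96 × √(0.358 × 0.642/263) = 0.058; 263 × 0.358 = 94.2; 263/0.358 = 734.6.

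**5. Effect on the acceptability analysis.** Under the test assumed in step 2, power with 94 respondents is about 0.49, against the stated 0.90.

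**The case against.** The strongest reply is that the working parts of Activity 2 are coherent and are about acceptability. The second questionnaire section, the sample size and the planned tests and regressions all serve that purpose. The objectives and methods speak only of associated factors, which the Analysis Plan ties to acceptability, and no model of hypertension status is specified. The explicit link to hypertension stands only in two forward-looking summaries and may be loose wording. Activity 3, the randomized trial, has its own eligibility, sample size and outcomes and does not use the prevalence estimate.

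Most of this stands, and it limits the point. A reader might infer that the whole of objective 2 fails. The document does not support that: acceptability and its correlates among known hypertensive attenders remain estimable. Nor does the article specify a model of hypertension status that is bound to fail; the fault is that a result is promised which this sample cannot supply.

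The reply does not rescue prevalence, which is stated as an aim throughout. It could be said that prevalence might come from health service records and the count of 14,322 active farmers in Panti. The document proposes no such ratio. The count covers one of the three areas, and a list of regular patients would miss undiagnosed and non-attending farmers. The split between grade I and grade II describes severity among cases and is not a prevalence.

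That the article is condensed is no answer either, since explicit eligibility criteria and an explicit sampling source contradict an explicit aim.

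**Conclusion.** The point holds in this form: the prevalence part of objective 2, and the factors associated with hypertension promised in the Abstract's Results paragraph and the Results section, cannot be estimated from the Activity 2 sample as described. The sample proportion with hypertension is 100% by construction and the number of non-cases is zero. This follows from the stated criteria and sampling source and needs no outside figure.

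The rest of Activity 2 and the inference of the randomized trial are unaffected. The half-widths and screening numbers rest on treating the Introduction's hypertension figures as prevalences. The power figures rest on the assumed comparison of 0.5 with 0.6. Both serve only to show the cost of the alternative design. The text should be corrected before the survey starts, because a stated aim cannot be met by the stated sample.

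**What to change.** **Preferred: reword.**
- Remove the prevalence aim from the Abstract (Objective, Methods, Results), the objectives at the end of the Introduction, the Study Overview, the Activity 2 Overview and the Results section.
- In the Abstract's Results paragraph and the Results section, change the promised factors from those associated with hypertension to those associated with acceptability of the plant-based diet.
- State that Activity 2 describes known hypertensive farmers attending Posbindu.

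The cost is editing only; sampling, sample size and analysis stay as they are.

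**If prevalence is to be kept: change the sampling frame before recruitment.**
- For the prevalence part, draw the random sample from all farmers aged 20-65 in the three health centre areas, regardless of blood pressure. Drop the third, fourth and fifth inclusion criteria for that part; the fifth, living with family for care, would also narrow the population.
- Determine hypertension status by the measurement procedure in the Activity 3 Data Collection Plan, which takes at least two readings, and record treatment status, since readings alone would miss treated farmers whose blood pressure is controlled.
- If factors associated with hypertension are wanted, add an analysis with hypertension status as the outcome.
- Restate the sample size for both purposes. At an assumed 35.8%, either accept about 94 hypertensive respondents and drop the 0.90 power claim for acceptability, or screen about 735 farmers to keep 263, before allowing for non-response.

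The cost is a new sampling list and, to hold the acceptability sample at 263, nearly three times as many farmers to contact (735/263 = 2.8).
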